### Endpoints of the study

#### Primary endpoints

Two primary endpoints of the study have been defined, represented by safety and efficacy of the treatment, respectively.Primary safety endpoint is to evaluate the safety of radiation therapy in the acute phase (during the first 30 days of the procedure) and at 3, 6, and 12 months. The incidence of serious adverse events related, or presumably related, to radioablation will be assessed as a percentage of the enrolled patients. Serious adverse events were the following:DeathCardio-circulatory arrestAcute myocardial infarctionCardiogenic shockPericarditis, myocarditis, and/or endocarditisAcute heart failureGastro-esophageal lesion (ulcer/stenosis/fistula/hemorrhage/perforation)Bronchopulmonary infectionInjury to the respiratory system (fistula/bronchial or tracheal stenosis, pulmonary fibrosis)Radio-induced oncogenesisPrimary efficacy endpoint is to evaluate the procedural effectiveness of therapy at 3, 6, and 12 months, represented by the total number of VT/VF episodes occurring after “blanking period,” compared with the period preceding the radioablation procedure (6 months).

VT episodes will be categorized as follows:VT episode > 30 s, regardless of the intervention of the ICDVT episode conditioning ICD intervention by means of “anti-tachycardia pacing” electrical therapy (without shock delivery)VT episode conditioning ICD shock intervention

The 6-week “blanking period” will start on the procedure day.

As a rule, pharmacological therapy, including antiarrhythmic drugs, will be maintained the same as before SBRT during the follow-up period. Changes of the pharmacological therapy will be determined only by specific clinical reasons.

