## Methods

The STRA-MI-VT trial was designed as spontaneous, experimental (phase Ib/II), prospective, open-label study. Fifteen patients are expected to be enrolled. The design of the study is illustrated in Fig. 1 and in Table 1.

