#### Eligibility criteria

The inclusion criteria are as follows:Patients with relapsing VT (at least 3 episodes of VT conditioning ICD intervention or VT with incessant or similar-incessant presentation) that has proved to be refractory to any form of pharmacological or non-pharmacological treatmentPatients with contraindication to conventional ablation, in relation to the high risk associated with the procedure for the type/severity of the condition of heart disease and/or presence of severe comorbidity; or alternatively, patients who have already undergone RF ablation in presence of an arrhythmogenic substrate refractory to previous ablation procedures or not suitable for any interventional approach,^1^ refusing any surgical ablative attempt because of a proven high operative risk, in relation to the patient’s characteristicsEjection fraction of the left ventricle ≥ 20%Age ≥ 50 yearsICD/subcutaneous ICD recipientsSigned informed consent

The exclusion criteria are as follows:Inability to express informed consent to participate in the studyPrevious thoracic radiotherapy with cardiac involvementActive myocardial ischemiaCardiac revascularization < 120 days.Non-correctable hemodynamic instability (cardiogenic shock, New York Heart Association (NYHA) IV)Comorbidity with prognosis < 12 months or other contraindications deemed significantPregnant women

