#### Secondary endpoint

Secondary endpoints are the following:Global mortality during follow-up (up to 12 months)Variations in the quality of life of patients in the follow-up (up to 12 months) with respect to the basal conditionChanges in cardiac function assessed by estimating the ejection fraction of the left ventricle on the echocardiographic examination in the follow-up (up to 12 months)

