### Statistical planning

#### Stopping criteria for ending the study

A study stopping rule based on the global rate of serious adverse events occurring within 30 days from the date of SBRT, that may be a consequence of the radioablation treatment (death, acute myocardial infarction, cardiogenic shock, cardio-circulatory arrest), will be adopted after enrollment of 5 patients. This rule will require the interruption of enrollment in the study if the observed adverse event rate will be higher than expected based on the data reported in the literature (at the time of study design) [12, 17–20]. Specifically, the reported rate (0 events out of 12 patients) is compatible with an estimated maximum frequency of 1 out of 5 events (upper limit of the 95% confidence interval). Therefore, the study will be stopped if ≥ 2 events occur within 30 days of the treatment carried out, among the first 5 patients treated.

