## Discussion

STRA-MI-VT is the first Italian spontaneous, experimental, prospective, open-label study testing the role of SBRT for the treatment of recurrent VT refractory to conventional therapies, in patients with structural heart disease.

In oncology, SBRT represents a well-established treatment modality that allows to noninvasively destroy cancerous cells by delivering multiple radiation beams. In the treatment of ventricular arrhythmias, radiation therapy is supposed to modify the arrhythmogenic substrate, by eliminating the heterogeneity responsible of the reentry mechanism, similarly to RF, thus reducing the episodes of VT. Differently from RF, SBRT allows to potentially ablate deep structures, which cannot be reached by catheters [29] and to accomplish the treatment in a noninvasive, faster, and safer manner [14].

On the other side, differently from standard ablation procedures, which lead to an immediate reduction of VT events, SBRT is supposed to manifest its therapeutic effects after months [29, 37]. Indeed, in the 6–8 week period following SBRT, corresponding to the “blanking period,” VT episodes may theoretically even be facilitated, given the complex maturation process of the lesion caused by SBRT [16–18, 21]. Moreover, the precise effect of high dose of radiation for the treatment of a structurally diseased heart is not well known; an additional concern is related to the possible wrong localization of target due to respiratory and cardiac motion: this could lead to target tissue underdosing and normal tissue overdosing, undermining both efficacy and safety of the treatment.

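### The primary safety rate counts a listed serious event only if it is attributed to radioablation, so in a study without a comparator that judgement partly sets the rate

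*Protocol article*

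**What the plan says.** Under Primary endpoints, the protocol article sets out to evaluate "safety of radiation therapy in the acute phase (during the first 30 days of the procedure) and at 3, 6, and 12 months". The measure is then fixed: "The incidence of serious adverse events related, or presumably related, to radioablation will be assessed as a percentage of the enrolled patients". The list that follows mixes two kinds of event. Some are fairly specific to radiation, such as gastro-esophageal lesions, bronchial or tracheal stenosis and fistula, pulmonary fibrosis and induced cancer. Others are common cardiac events: death, arrest, infarction, cardiogenic shock and acute heart failure.

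On the design, Methods says: "The STRA-MI-VT trial was designed as spontaneous, experimental (phase Ib/II), prospective, open-label study". It adds: "Fifteen patients are expected to be enrolled". No comparator arm is described. Under Eligibility criteria, one route into the study is that standard catheter ablation has been ruled out, which the criterion words thus: "in relation to the high risk associated with the procedure for the type/severity of the condition of heart disease and/or presence of severe comorbidity". The ejection fraction may be as low as 20%.

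The Discussion states that "the precise effect of high dose of radiation for the treatment of a structurally diseased heart is not well known". Under Secondary endpoint, the one listed safety event that is also counted regardless of cause is death: "Global mortality during follow-up (up to 12 months".

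The stopping rule, under Stopping criteria for ending the study, refers to a global rate of four event types within 30 days, but describes them as events "that may be a consequence of the radioablation treatment".

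**The concern.** A safety incidence restricted to related events can be interpreted when relatedness can be established with some confidence. Here that is difficult for several items on the list. A non-fatal arrest or an episode of acute heart failure in a patient with structural heart disease and refractory arrhythmia may be disease progression or treatment harm. No concurrent group shows how often such events would have happened anyway, and the article itself says that knowledge of the treatment's cardiac effect is limited.

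If a treatment-caused event is judged to be disease, it leaves the primary safety numerator, and the rate moves in the direction of the trial's hypothesis that the treatment is safe. The article names no endpoint that tallies non-fatal arrest, infarction, shock or heart failure regardless of cause. A reader of the results would then be unable to see how much of the primary figure rests on attribution.

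**Working it through.** **The plan's own safety figure.** The only safety number in the article is in the stopping rule: 0 events in 12 patients, said to be compatible with at most 1 in 5.
- One-sided exact 95% upper limit: 1 − 0.05^(1/12) = 22.1%, or 5 × 0.221 = 1.10 patients in 5.
- Two-sided exact 95% upper limit: 1 − 0.025^(1/12) = 26.5%, or 5 × 0.265 = 1.32 patients in 5.

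Read as a whole number of patients in five, 1 in 5 is reasonable. The present point neither uses nor overturns this figure.

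**Inputs for the primary endpoint.** The denominator is the enrolled patients, planned as 15 (Methods). The numerator is patients with a listed event judged related or presumably related (Primary endpoints). The article gives no background rate of the listed events and no expected share judged related, so the event counts below are assumptions for illustration.

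**Effect of one decision.** 1/15 = 6.7 percentage points.

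**Range from the same clinical course.** Suppose 3 of 15 patients have a listed event. Intervals are exact (Clopper-Pearson) 95%; for zero events the upper limit is 1 − 0.025^(1/15) = 21.8%.

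| Judged related | Rate | Exact 95% CI |
|---|---|---|
| 3 of 15 | 20.0% | 4.3 to 48.1 |
| 2 of 15 | 13.3% | 1.7 to 40.5 |
| 1 of 15 | 6.7% | 0.2 to 31.9 |
| 0 of 15 | 0% | 0 to 21.8 |

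With 6 patients affected instead of 3, the range runs from 6/15 = 40.0% (16.3 to 67.7) down to 0%.

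**Stopping rule, if its count were filtered in the same way.** The rule stops the study at 2 or more events in the first 5 patients. With per-patient event probability p, P(2 or more of 5) = 1 − (1−p)^5 − 5p(1−p)^4. Assume a true 30-day rate of 20%.
- All events counted, p = 0.20: 1 − 0.328 − 0.410 = 26.3%.
- Half judged related, p = 0.10: 1 − 0.590 − 0.328 = 8.1%.

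These two values show only that the ambiguity matters. They do not show that the rule is filtered.

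**The case against.** Counting related or presumably related events is conventional in early-phase work, and the article describes a phase Ib/II study. Presumably related is an inclusive threshold, so doubtful events can be counted. An all-cause count does not separate harm from disease either: without a comparator it certainly includes some disease. The article also describes earlier series in terms of attribution. In one 19-patient trial, heart failure exacerbation and pericarditis were put down to the treatment, so attribution does not always lean towards disease. These arguments stand as reasons to keep the related subset visible. They do not remove the dependence on judgement, which an all-cause count avoids.

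Four stronger readings are tempting, but the article does not support them.

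- *The patients are end-stage, so harm and disease always look alike.* Cardiogenic shock or NYHA class IV that cannot be corrected, active ischemia, recent revascularization and comorbidity with a prognosis under 12 months are all excluded. Part of the event list is also fairly specific to radiation.
- *Events judged to be disease disappear from every endpoint.* VT/VF episodes after the blanking period are counted for efficacy with no attribution filter, ejection fraction is a secondary endpoint, and an event-free survival curve is planned, although its event is not named. Adverse effects are evaluated through 12 months in Table 1. What is missing is a named all-cause tally of the non-fatal listed events.
- *Attribution will be made without independent review.* The article does not say who attributes or by what rule, and the full protocol may. Independent review would make the judgements more consistent, but it could not supply a comparator.
- *The stopping rule is filtered by attribution.* The causal phrase may simply describe the four event types, and the operative sentence on two or more events carries no filter. The wording is ambiguous and no more than that.

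**Conclusion.** The point holds as a weakness in how the primary safety endpoint is fixed. Because the restriction to related events is written into the endpoint, an analysis plan could add adjudication but could not turn the measure into an all-cause count. Attribution partly determines the rate, at 6.7 percentage points per patient of 15, and among the listed events only death has a named all-cause endpoint.

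A reader might infer from the 20% and 0% illustration that the safety conclusion would reverse. It would not. The intervals 4.3 to 48.1 and 0 to 21.8 overlap, and the article sets no safety threshold or formal safety test at 15 patients. What changes is the reported figure.

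The size of the effect in practice is unknown, because it depends on the number of listed events and the share attributed to treatment, and the article gives neither. The conclusion rests on there being no comparator, as the article describes the design, and on several listed cardiac events having both disease and treatment as plausible causes.

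**What to change.** Report the proportion of enrolled patients with any listed serious event, regardless of attributed cause, at 30 days and at 3, 6 and 12 months, with exact 95% confidence intervals. Make this the headline primary safety figure, or report it together with the present one, and show the related or presumably related subset beside it. Keeping enrolled patients as the denominator leaves that part of the definition unchanged.

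In the stopping criteria, reconcile the reference to a global rate with the phrase about consequence of treatment, so that it is clear whether the count is filtered by attribution.

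No extra visits are needed, since adverse effects are already evaluated at each stage. The all-cause figure will include background disease events and look less favourable, and the text should say so. Recruitment had begun in September 2019 and four patients had been treated when the article was submitted. Replacing the headline measure would therefore change a primary endpoint during the trial and would need a dated amendment. Adding the all-cause figure alongside the present one is the lighter change and achieves most of the benefit.

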**Methods:**

This is a spontaneous, prospective, experimental (phase Ib/II), open-label study (NCT04066517); 15 patients with structural heart disease and intractable VT will be enrolled within a 2-year period. Advanced multimodal cardiac imaging preceding chest CT-simulation will serve to elaborate the treatment plan on different linear accelerators with target and organs-at-risk definition. SBRT will consist in a single radioablation session of 25 Gy. Follow-up will last up to 12 months.

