### Follow-up

Adverse effects will be classified according to the international Common Terminology Criteria for Adverse Events v 5.0/CTCAE document.

A follow-up phone-call will be performed once a week for the first 4 weeks after SBRT.

Regular cardiological follow-up visits, including 12-lead ECG and ICD interrogation, will be performed 3, 6, and 12 months after SBRT. Echocardiography examination and SF-36 health questionnaire will be provided 3, 6, and 12 months after SBRT. Patients will be visited by a radiation oncologist, and thorax CT will be performed 3 and 12 months after SBRT.

Pharmacological therapy, including antiarrhythmic drugs, will be maintained the same as before SBRT during the entire follow-up.

With regard to the early post-SBRT phase and the possible occurrence of transient processes impacting on cardiac arrhythmogenicity, accordingly to literature [16–18, 21], a 6-week “blanking period,” starting immediately after SBRT treatment, will be considered in the analysis of VT recurrences during follow-up.

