#### Calculation of the target sample size and statistical analysis

A sample of 15 patients will allow a 60% reduction in ventricular arrhythmic episodes to be assessed as significant (*p* < 0.05), assuming an average of 10 episodes in the 3 months preceding the procedure, with a statistical power of 90%. Continuous variables will be expressed as mean ± standard deviation or median and interquartile range variables with non-normal distribution, and discrete variables as absolute numbers and percentages. Primary efficacy endpoint (reduction of ventricular arrhythmic episodes) and secondary endpoints (clinical, echocardiographic, and psychometric characteristics) will be evaluated with the Student’s *t* test for paired data (continuous variables with normal distribution) or with the Wilcoxon sign rank test (variables with non-normal distribution). Kaplan-Meyer curves will be developed for event-free survival analysis at follow-up. All tests will be two-tailed and a *p* < 0.05 will be considered significant.

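### The late safety percentage is taken over all enrolled patients, so anyone who withdraws or misses the month-12 assessment counts, in effect, as free of late radiation harm

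*Protocol article*

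**What the plan says.** Safety is one of two primary endpoints (protocol article, Primary endpoints). It is to be evaluated "in the acute phase (during the first 30 days of the procedure) and at 3, 6, and 12 months". The measure is fixed in the next sentence: "The incidence of serious adverse events related, or presumably related, to radioablation will be assessed as a percentage of the enrolled patients". Planned enrolment is 15 (Abstract, Methods: "15 patients with structural heart disease and intractable VT will be enrolled within a 2-year period").

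The list of qualifying events includes harms that can appear late, among them pulmonary fibrosis, airway stenosis or fistula, gastro-oesophageal stenosis or fistula, and radiation-induced cancer. The Follow-up section sets the assessments best placed to find several of these: "Patients will be visited by a radiation oncologist, and thorax CT will be performed 3 and 12 months after SBRT". Table 1 agrees. It also schedules an adverse-effects evaluation at every follow-up point, including month 6.

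Death is on the event list, but the lead sentence counts only events attributed or presumably attributed to the treatment. All-cause mortality up to 12 months is a separate secondary endpoint. The statistical section adds that Kaplan-Meier "curves will be developed for event-free survival analysis at follow-up". It does not define the event or link the curves to the safety endpoint.

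**The concern.** A single fixed denominator suits the 30-day rate, when nearly every patient is under observation. It suits month 12 less well. A patient who withdraws after month 3, or does not attend at month 12, has no second CT and no second radiation-oncology visit. Late harm in that patient cannot enter the numerator by that route, yet the patient stays in the denominator. The reported percentage falls as more patients go unassessed.

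The trial is partly justified by the uncertain long-term safety of the technique (Analysis of previous experiences). The Conclusions foresee wider use if the primary endpoints are met. A late rate that improves with missing data would support that step for the wrong reason. Some attrition is plausible: patients have refractory VT, may have an ejection fraction as low as 20%, and may have severe comorbidity.

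This point is separate from whether enrolled but untreated patients belong in the denominator. It would remain if the denominator were changed to treated patients.

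**Working it through.** **Inputs.** N = 15 (Abstract; Methods). Time points and denominator come from Primary endpoints, and CT and radiotherapy visits at months 3 and 12 from Follow-up and Table 1. The plan states no expected late-event rate and no attrition, so there is no figure to reproduce. The number lost, k, is my assumption, shown from 1 to 5.

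**Step 1: withdrawals and missed visits.** Let x be the related events seen. The plan reports x/15 whatever k is. If the k patients are lost before any late event could be seen and have the same risk as the rest, the estimate is x/(15-k). The ratio of the two is (15-k)/15:

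- k = 1: 14/15 = 0.93
- k = 3: 12/15 = 0.80
- k = 5: 10/15 = 0.67

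For three events, with exact (Clopper-Pearson) 95% intervals:

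- plan's rule: 3/15 = 20.0% (4.3 to 48.1)
- k = 3: 3/12 = 25.0% (5.5 to 57.2)
- k = 5: 3/10 = 30.0% (6.7 to 65.2)

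**Step 2: no events seen.** The exact two-sided 95% upper limit is 1 - 0.025^(1/n):

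- n = 15: 21.8%
- n = 12: 26.5%
- n = 10: 30.8%

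**Step 3: events seen before patients leave.** The factor in Step 1 is the largest understatement under its assumptions, because events found earlier still count. Suppose one event is found at month 3, three event-free patients then withdraw, and two events are found at month 12. At month 12, 15 - 1 - 3 = 11 patients are at risk. With withdrawals censored, the cumulative incidence is 1/15 + (14/15)(2/11) = 39/165 = 23.6%. The plan's rule gives 3/15 = 20.0%, a factor of 0.85.

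**Step 4: unrelated deaths.** Take the same pattern, but let the three patients die of another cause. With death as a competing event, the probability of being alive and event-free just before month 12 is 1 - 1/15 - 3/15 = 11/15. The cumulative incidence is 1/15 + (11/15)(2/11) = 3/15 = 20.0%, exactly the plan's percentage. Only harm that had arisen after month 3 but had not been detected before death is missed.

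**Step 5: if loss is related to harm.** The extreme is that all k lost patients had late harm, giving (x+k)/15. With x = 3 this is 6/15 = 40.0% for k = 3 and 8/15 = 53.3% for k = 5.

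**The case against.** The strongest objection concerns deaths. A reader might infer that every patient who dies of another cause is wrongly counted as unharmed, and that the 0.80 to 0.67 factor applies to deaths as well. The documents do not support that. Step 4 shows that events over N is then a legitimate crude cumulative incidence. A death judged related counts as an event, and so does a related event recorded before death. The attrition one would expect from this population's severity is mainly death, so the full factor cannot be justified by mortality.

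Detection is also better than a glance at the CT schedule suggests. The month-3 CT and the month-6 adverse-effects evaluation can catch earlier and symptomatic harm. Eligibility excludes comorbidity with a prognosis under 12 months, which should limit attrition. These points narrow the gap but do not close it for harm that needs the month-12 CT or visit.

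It can also be said that handling of withdrawals belongs in an analysis plan that is not shown. That would hold if the article were silent, but it states the denominator. The Kaplan-Meier sentence does not replace that rule, because its event is undefined.

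Finally, the endpoint has no safety threshold, test or interval, and the only formal stopping rule uses 30-day events in the first five treated patients. No decision rule is therefore altered, and the upper limits above are my calculation, not figures the plan commits to. The intervals at this sample size overlap heavily. All of this stands and limits the weight of the point.

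**Conclusion.** The concern holds for loss to follow-up. At 3, 6 and above all 12 months, the stated rule gives a safety percentage biased downward when patients withdraw or miss assessments. For unrelated deaths the rule is sound, except that it can hide harm that only the month-12 CT or visit would have shown.

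The size depends on k, which the documents do not give. One lost patient gives a factor of about 0.93. Three to five, taken as an illustration, give 0.80 to 0.67. These factors assume that the lost patients have the same risk as the rest and that none of their late harm was seen before they left. Earlier detection makes the bias smaller, and loss related to harm makes it larger. The 30-day rate is little affected. The change is worth making because this is a primary endpoint in 15 patients and each unassessed patient moves the result towards apparent safety.

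**What to change.** In Primary endpoints, keep the simple n/N for 30 days. For 3, 6 and 12 months, report the cumulative incidence of a first listed related event, counted from the SBRT date. Censor patients who withdraw, or are no longer assessed, at their last assessment, and treat unrelated death as a competing event.

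That estimate does not recover harm undetected at death. So, for events found by thorax CT or at the radiotherapy visit, also give the number assessed at each visit and the events over patients assessed, with an exact 95% interval. Keep events found at earlier visits, so that a patient with fibrosis on the month-3 CT who later dies is not dropped. Label this figure as conditional on being alive and assessed, because it answers a different question from the cumulative incidence.

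The change is to analysis wording only and needs no new visits or data. The cost is a somewhat higher late rate and a wider interval.

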Of note, different cellular processes are involved in the mechanism of action of radioablation; the therapeutic effect of SBRT is supposed to arise basically from the induction of cellular death and transmural fibrosis that leads to the abolishment of abnormal conduction/automaticity in the myocardial tissue responsible of the arrhythmia [16, 17]. Fibrosis maturation is however progressive and requires several weeks to complete, so that in the intermediate phase, other factors, including acute inflammation and vascular injury, may impact on short-term outcome [16, 18].

Recently, SBRT has been used for the treatment of 35 patients with VT [13, 19–30]. SBRT, guided by imaging techniques partially integrated by electrocardiographic and/or electroanatomical data, significantly reduced in these patients the arrhythmic burden, in the absence of major adverse events correlated with the treatment applied.

Based on these evidences, we designed a spontaneous, prospective, experimental (phase Ib/II), open-label study to validate efficacy and safety of SBRT in a well-defined cohort of patients with recurrent VT not eligible to conventional catheter ablation.

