**Fig. 1 Fig1:**
[figure not shown]
Flowchart of STRA-MI-VT study. Legend: CT, computed tomography; ECG, electrocardiogram; OARs, organs at risk; QoL, quality of life; SBRT stereotactic body radiotherapy; VT ventricular tachycardia

**Table 1 Tab1:** Planning of the study activities

		Study phases							
		Screening and enrolment	Pre-treatment	Radioablation	Post-treatment (until discharge)	1 month FU	3 months FU	6 months FU	12 months FU
Study activities	Compliance with inclusion/exclusion criteria	X							
	Informed consent	X							
	Anamnesis		X						
	Physical examination		X		X				
	Laboratory tests		X		X				
	Thorax RX		X						
	Echocardiogram		X		X		X	X	X
	12-lead ECG		X		X		X	X	X
	ICD interrogation		X	X	X		X	X	X
	Other routine patient-related exams		X		X				
	QoL evaluation		X				X	X	X
	Cardiac CT		X						
	Electroanatomical mapping		X^*^						
	Simulation thorax CT and target and OARs definition		X						
	Treatment planning elaboration		X						
	Radioablation			X					
	Weekly phone contact					X			
	Cardiological visit				X		X	X	X
	Radiotherapy visit						X		X
	Thorax CT						X		X
	Adverse effects evaluation			X	X	X	X	X	X

^*^To be performed unless already in possess of necessary diagnostic information

*CT* computed tomography; *ECG* electrocardiogram; *FU* follow up; *ICD* implantable cardioverter defibrillator; *QoL* quality of life; *RX* radiography

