### Pre-treatment evaluation

Patients will preliminarily undergo the complete diagnostic workup defined for patients with an indication to conventional VT catheter ablation. In agreement with our ordinary practice, electroanatomical mapping (EAM) combined with cardiac computed tomography (CT) will represent the first choice of imaging to identify the arrhythmia substrate and to define the target area.

The patients’ quality of life will be evaluated using the Short Form-36 (SF-36) health questionnaire.

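### The primary safety rate is divided by enrolled patients, but only treated patients can have a radioablation event, so anyone enrolled and not treated lowers it

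*Protocol article*

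**What the plan says.** In the protocol article, the Primary endpoints section takes as the safety measure "The incidence of serious adverse events related, or presumably related, to radioablation" and states that it "will be assessed as a percentage of the enrolled patients". The acute window in the same section is 30 days counted from the procedure, not from enrolment.

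On numbers, the Methods section says: "Fifteen patients are expected to be enrolled".

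Table 1 separates the phases. The first is "Screening and enrolment", which holds the eligibility check and informed consent. A pre-treatment phase follows with cardiac CT, electroanatomical mapping (unless the information already exists), simulation CT, target definition and planning. Radioablation is the third phase, and the evaluation of adverse effects starts there. The Pre-treatment evaluation section agrees with this order: "Patients will preliminarily undergo the complete diagnostic workup defined for patients with an indication to conventional VT catheter ablation".

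The section on stopping criteria brings its rule into force once five patients are enrolled, but counts events "among the first 5 patients treated".

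**The concern.** The numerator and the denominator refer to different groups. An event can be related to radioablation only in a patient who received it. A patient who consents and then deteriorates, dies or cannot be planned before the session adds one to the denominator and can add nothing to the numerator.

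Such losses are plausible here. The eligibility criteria admit incessant or refractory VT, an ejection fraction down to 20% and severe comorbidity, and the work-up after enrolment can include invasive mapping and needs a panel's consensus on the target. The article does not say that enrolled means treated, nor that untreated patients are replaced.

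At stake is a primary endpoint in a sample of 15, where one or two patients visibly move a percentage. Any error has one direction, towards a lower apparent event rate.

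**Working it through.** The article states no value for this incidence, so there is no figure of its own to reproduce. The check concerns how the stated denominator behaves.

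**Inputs**

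- Enrolled: 15 (Methods).
- Numerator: patients with a listed event related or presumably related to radioablation (Primary endpoints).
- Enrolled but not treated, *m*: not given. The range 0 to 5 is an assumption. Study organization and status reports four patients who underwent SBRT, but not how many had been enrolled by then, so it gives no estimate of *m*.

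**Formulas**

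- With *x* patients having an event, the rate as written is *x*/15 and the rate among treated patients is *x*/(15 − *m*).
- The ratio of the first to the second is (15 − *m*)/15, that is, number treated over number enrolled. It does not depend on *x*.
- With no events among *n* patients, the exact (Clopper-Pearson) two-sided 95% upper limit is 1 − 0.025^(1/*n*).

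**Results**

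| Not treated | Treated | Factor | 2 events, as written | 2 events, among treated | 0 events, upper limit as written | 0 events, upper limit among treated |
|---|---|---|---|---|---|---|
| 0 | 15 | 1.00 | 13.3% | 13.3% | 21.8% | 21.8% |
| 1 | 14 | 0.93 | 13.3% | 14.3% | 21.8% | 23.2% |
| 2 | 13 | 0.87 | 13.3% | 15.4% | 21.8% | 24.7% |
| 3 | 12 | 0.80 | 13.3% | 16.7% | 21.8% | 26.5% |
| 4 | 11 | 0.73 | 13.3% | 18.2% | 21.8% | 28.5% |
| 5 | 10 | 0.67 | 13.3% | 20.0% | 21.8% | 30.8% |

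For example, with three untreated, 2/15 = 13.3% as written and 2/12 = 16.7% among treated patients; with no events, 1 − 0.025^(1/15) = 21.8% and 1 − 0.025^(1/12) = 26.5%.

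As written, the rate and its limit stay the same down the table, while the quantity of interest, the risk after treatment, rises.

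**The two safety denominators side by side.** The primary endpoint divides by enrolled patients. The stopping rule counts events in treated patients but starts from the number enrolled. If any enrolled patient is not treated, the fifth enrolment and the fifth treatment are different moments, and the two safety statements describe different groups.

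**The case against.** The strongest reply is that the article uses enrolled loosely to mean treated. The stopping rule passes from five enrolled to five treated as if they were the same. The Treatment section speaks of choosing the accelerator for each enrolled patient. The review of earlier experience describes the treatment outcomes of another trial by its number enrolled. The acute window also starts at the procedure. On that reading the investigators already mean a treated denominator, and only the word is wrong.

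This reading is plausible, and it makes the point a matter of clarification as much as of correction. It does not remove the literal rule. Table 1 makes enrolment a phase of its own, two steps before radioablation, and no passage equates the terms. Nor is this a detail simply left to an analysis plan: the denominator is stated, so a plan that used a treated set would contradict the published endpoint.

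A second reply is that the effect is small beside the sampling error. This stands. With two events and one untreated patient, 13.3% becomes 14.3%, while the exact upper limit for 2/15 is already 40.5%. But sampling error is shown by an interval and falls on both sides, whereas dilution is not shown and has one direction.

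A third reply concerns attribution. Because the numerator depends on a judgement of relatedness in an open-label study, a reader might infer that deaths put down to the underlying disease would go unreported. The documents do not support that: all-cause mortality to 12 months is a secondary endpoint, and presumably related events are included. What remains is that the article does not expressly plan to tabulate the listed non-fatal events regardless of attribution.

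**Conclusion.** The point holds in conditional form. As stated, the primary safety incidence is the rate among treated patients multiplied by the number treated over the number enrolled. Under the assumed range of 0 to 5 untreated out of 15, the factor is 1.00 to 0.67. The article gives no attrition before treatment, so the actual size is unknown and may be zero. The point merits correction because it affects a primary endpoint and costs almost nothing to repair, not because a large bias has been shown.

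Three stronger readings are tempting, and the documents do not support them.

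- A reader might infer that the safety figure is biased as a matter of fact. It is biased only if someone enrolled is not treated.
- A reader might set the 21.8% upper limit for 0/15 against the 1 in 5 in the stopping criteria. That figure concerns four event types within 30 days; the primary endpoint has ten categories followed to 12 months. They are not comparable.
- A reader might infer from the same 21.8% that the aim "to validate efficacy and safety of SBRT" cannot be met. That is a comment on sample size. It assumes that all 15 are treated, which is the case without dilution. The endpoint itself speaks only of evaluating safety, and the abstract's objective of investigating it.

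**What to change.** 1. In Primary endpoints, make all patients who receive any SBRT the denominator of the safety incidence, at 30 days and at 3, 6 and 12 months.
2. Report separately the number enrolled but not treated.
3. In the stopping criteria, reconcile the use of enrolled for when the rule applies with the use of treated for what it counts, so that the safety statements refer to one defined group.
4. Optionally, tabulate the listed non-fatal events regardless of attribution beside those judged related. All-cause death is already covered by the secondary endpoint.

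The cost is a change of wording and one extra reported count, plus a table column if the optional step is taken. The reported rate may become slightly less favourable. Patient care and data collection are not affected.
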